### Data storage and management

For data storage and management, we use the national imaging platform provided by CTMM/Lygature TraIT (http://www.ctmm-trait.nl/trait-tools/xnat). This platform is built on top the open source XNAT software (www.xnat.org). Users need proper authorization in order to access images and derived data, this to secure patients data. The Clinical Trial Processor software is used to transfer data from the local PACS software to the central imaging platform. Readers of the SMS will enter their findings separately into a standardized and anonymized clinical report form in the online clinical software program Castor EDC.

### Statistical analysis

The sensitivity, specificity, positive predictive value, and an estimated negative predictive value of the SMS and US for the detection of HCC will be calculated and compared, using the results of the full MRI liver protocol as reference standard, combined with negative follow-up for the cases of no suspicious findings at US and SMS. Only an estimated negative predictive value can be calculated, due to non-availability of the full liver MRI in case of no findings on both the US and SMS. McNemar test will be used to determine significance in differences between the sensitivity and specificity of SMS *versus* US.

The cost-effectiveness analysis will be conducted from a healthcare perspective, using costs per detected cancer as outcome. Direct medical costs will be measured for both diagnostic pathways, using collected data from participating medical center databases and literature. The analysis will be carried out according to Dutch guidelines and by using a Markov model. The final outcome will be an incremental cost-effectiveness ratio to express the difference in costs between the SMS and US pathway per unit of health gain, *i.e.*, the number of detected cancer and quality adjusted life years. The uncertainty around the estimates will be addressed using deterministic and probabilistic sensitivity analyses.

In addition, data from this study and literature will be used to calculate the impact of improved detection of early-stage HCC on outcomes, *i.e.*, progression free survival and overall survival.

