### Sample size calculation

The sample size was determined using a procedure of 1000 simulations. Based on own preliminary results and previously reported prevalence, the prevalence of HCC in our screening population was set at 12% [17–19]. Secondly, the sensitivity and specificity of the SMS protocol was assumed be 80% and 72%, respectively, based on our own data analysis [15]. For US, the sensitivity and specificity were assumed to be 53% and 91%, respectively [8, 15]. Then, the number of true and false positives and true and false negatives were generated. Using exact binomial testing, the *p*-value from comparing US and SMS was obtained. Next, this procedure was repeated by generating 1000 datasets and investigating the proportion of samples with *p*-value below 0.05 (α-level). Finally, the sample size was determined by setting the power (1-β) at 80%. This resulted in a calculated sample size of 470 assuming a drop-out rate of 10–15%.

Furthermore, given the dynamic enrollment of the participants, we estimated that the average number of screenings will be 2.5 per patients. Using the calculated sample size, the total number of screenings over the study period will be 1,175 screenings of paired US-SMS. In addition, similar prospective studies have been carried out with comparable numbers [18, 19]. Therefore, our study cohort will have a sufficient sample size to evaluate the value of the SMS and relate to other similar studies.

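### Absolute sensitivity depends on the same unseen false negatives as NPV, yet only NPV is labelled an estimate

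*Protocol article*

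**What the plan says.** Under Imaging criteria for suspicious HCC lesions and confirmation, the protocol article sends a patient to the full liver MRI only after a suspicious US or SMS, with CT as the alternative. A screening that is negative on both tests gets neither.

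The Statistical analysis section takes the full MRI as reference standard, "combined with negative follow-up for the cases of no suspicious findings at US and SMS". It then notes: "Only an estimated negative predictive value can be calculated, due to non-availability of the full liver MRI in case of no findings". The same section and the Endpoints section each list four accuracy measures. In both lists NPV is called estimated, while sensitivity, specificity and PPV carry no qualifier. Sensitivity and specificity are to be compared with the McNemar test.

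On the amount of follow-up, the Sample size calculation section says: "we estimated that the average number of screenings will be 2.5 per patients". With 470 patients this gives 1,175 paired screenings.

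**The concern.** The reason given for calling NPV an estimate is that double-negative screenings have no full MRI, so HCC missed by both tests is not seen directly. Those missed tumours are false negatives of each test. They belong in the denominator of sensitivity just as they belong in the denominator of NPV, so the reason applies equally to sensitivity, which is left unqualified.

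Absolute sensitivity is the first-named component of the primary endpoint. A reader would set the reported SMS figure beside the pilot range of 80–97% and the US figure beside the 47% cited in the Background, without being told that both could be too high. The absolute difference between the tests is stretched in the same way.

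**Working it through.** **Inputs (Sample size calculation).** "the sensitivity and specificity of the SMS protocol was assumed be 80% and 72%, respectively". "For US, the sensitivity and specificity were assumed to be 53% and 91%, respectively". Prevalence is 12%, N is 470, alpha is 0.05 and power is 80%; the test is described as "Using exact binomial testing". Two quantities are not stated and are varied here: the overlap of the two tests' misses, and the share of double-missed HCC that follow-up recovers.

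**The plan's own figures.** 470 × 2.5 = 1,175, as stated. Simulating a two-sided exact test on discordant pairs, with HCC count Binomial(470, 0.12), sensitivities 0.80 and 0.53, and independent tests, gives power 0.81 if all 470 are evaluable. The planning inputs are therefore read as the plan intended. Two-sidedness and independence are assumptions.

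**Share of HCC missed by both tests, u.**
- Independent misses: u = 0.20 × 0.47 = 0.094.
- Full overlap (every HCC missed by SMS is also missed by US): u = 0.20.
- Lowest possible: u = 0, if the tests never miss the same HCC.

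Expected HCC: 470 × 0.12 = 56.4. Missed by both at a given screening: 56.4 × 0.094 = 5.3 to 56.4 × 0.20 = 11.3.

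**Apparent sensitivity.** Let f be the share of double-missed HCC that follow-up recovers and counts back as a miss. Then apparent sensitivity = true sensitivity / (1 − u(1 − f)).

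| Misses | f | Denominator | SMS (true 80%) | US (true 53%) | Difference (true 27) | Ratio |
|---|---|---|---|---|---|---|
| Independent | 0 | 0.906 | 88.3% | 58.5% | 29.8 | 1.51 |
| Independent | 0.5 | 0.953 | 83.9% | 55.6% | 28.3 | 1.51 |
| Full overlap | 0 | 0.800 | 100% | 66.3% | 33.8 | 1.51 |
| Full overlap | 0.5 | 0.900 | 88.9% | 58.9% | 30.0 | 1.51 |
| Any | 1 | 1.000 | 80% | 53% | 27.0 | 1.51 |

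**Comparison with the measure that is flagged** (independent misses, f = 0). Per patient, the double-missed share is 0.12 × 0.094 = 0.01128.
- NPV, SMS: true 0.6336/0.6576 = 96.4%; apparent (0.6336 + 0.01128)/0.6576 = 98.1%.
- NPV, US: true 0.8008/0.8572 = 93.4%; apparent (0.8008 + 0.01128)/0.8572 = 94.7%.
- Specificity, SMS: 0.64488/0.89128 = 72.4% against 72%.
- Specificity, US: 0.81208/0.89128 = 91.1% against 91%.

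NPV moves by 1.7 and 1.3 points and sensitivity by 8.3 and 5.5. The measure without the label moves more. Specificity moves by less than 1 point, also under full overlap (72.7% and 91.2%).

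**Double-negative last screenings.** P(both negative) = 0.88 × 0.72 × 0.91 + 0.12 × 0.094 = 0.588 under independence. Each patient has one last screening: 470 × 0.588 = 276, and 276/1,175 = 24%. These pairs have no later paired study screening that could expose a miss.

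**What is not affected.** HCC missed by both tests is a concordant pair and does not enter the McNemar statistic. In the ratio of sensitivities, and in the ratio of false-positive rates (0.28/0.09 = 3.11 at planning values), the unknown denominator cancels because test-positives go to the reference standard.

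**The case against.** The strongest reply is that double negatives are not left without a reference. Negative follow-up is part of the reference standard, screening repeats every 6 months, and both tests flag new or growing nodules, so a lesion missed once may be found later. Patients come from existing US surveillance cohorts, and nothing confines follow-up to paired study screenings. The detail of that follow-up may stand in a fuller document. This reply stands as to size: the rows with f = 0 are the upper end for each overlap, not a forecast. It does not remove the point. Follow-up serves NPV in the same way, and the plan still calls NPV estimated.

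Several stronger readings are tempting but not supported:
- A reader might take the sentence on NPV as a claim that nothing else is affected. Its more natural sense is that NPV can be no more than an estimate. The fault is the missing qualifier on sensitivity in both lists.
- A reader might infer that 470 of 1,175 pairs (40%) lack any later examination. That counts every last screening, including positive ones, which go to full MRI or CT. At planning values under independence the figure is 276 (24%).
- A reader might conclude that the comparison of SMS with US is invalid. The McNemar test and the ratio are unaffected.
- A reader might suppose that the inflated sensitivities go into the Markov model. The article does not say which sensitivities the model uses, and it commits to sensitivity analyses there.

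**Conclusion.** The point holds for the absolute sensitivities of both tests. HCC missed by both and not recovered can only push them upwards. There is no inflation only if follow-up recovers every double miss and counts it as one, or if the tests never miss the same tumour.

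The direction is firm and the size is not. Across no recovery to half recovery, and independent misses to full overlap, apparent SMS sensitivity runs from 83.9% to 100% against a true 80%, and US from 55.6% to 66.3% against a true 53%. These ranges rest on the planning values and on assumed overlap and recovery. The significance test between the tests, their sensitivity ratio and, for practical purposes, specificity stand as planned. This should be corrected, but it does not threaten the paired design.

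**What to change.** In the Statistical analysis section, with matching words in Endpoints:

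1. Call absolute sensitivity estimated, for the same reason as NPV. For specificity, a note that the effect is under 1 point at planning values is enough.
2. Report each test's sensitivity over a stated range of double-missed, unrecovered HCC, for example by the formula above.
3. Report the relative true-positive rate and the relative false-positive rate, each with a 95% CI, beside the McNemar test. Making these ratios the primary effect measures is optional.
4. Apply the negative-follow-up rule to each patient's last double-negative screening as well, using routine surveillance records where available, and count a recovered HCC as a miss at the earlier screening. A fixed window would make the rule cleaner, but its length is for the investigators to choose.

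No additional imaging is needed. The cost is analysis work, a record check after the last paired screening, a less favourable range for sensitivity and possibly later final reporting.

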## Methods

### Study design

The study protocol was reviewed and approved by the Medical Ethics Review Committee (MEC-2022-0731). Written informed consent will be signed and obtained from all participating patients by the investigators. This trial is registered at the international trial registry of ClinicalTrials.gov (NCT05429190).

This is a prospective, multicenter, observational patient cohort study. Patients will be recruited from the already existing US surveillance cohorts of six hospitals in the Netherlands. Patients will be invited for paired US-SMS surveillance, every 6 months (Fig. 2).

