### Surveillance program

Patients enrolled into the study receive paired US-SMS surveillance with a 6-month interval, with an inclusion period of 3 years. The US surveillance will be performed by radiologists or hepatologists with at least 3 years of experience with US of the liver and upper abdomen on current clinical applied ultrasound systems. Participating centers have different brands of US systems with a model build 0.5 to 6 years ago. Reading of the US will be done by one reader who will also evaluate the SMS as one of three readers.

MRI will be performed on clinical applied 1.5-T system from different vendors using a dedicated body coil with an 8–16 channel range. The SMS will consist of three sequence parameters as specified in Table 2. Each SMS will be evaluated by three experienced and well-trained radiologists who will be blinded for each other’s findings and of which two readers will also be blinded for US findings.

**Table 2 Tab2:** Scan parameters of the short MRI surveillance (SMS) protocol on 1.5-T systems

Sequence	Matrix size	Slice thickness (mm)	Gap (mm)	Repetition time (ms)	Echo time (ms)	Flip angle (°)	Duration (min:s)
Axial, T1-weighted 3D gradient-echo in-out phase	300 × 260	4	0	6.2	2.1/4.2	12	0:16
Axial, T2-weighted fast spin-echo with fat saturation	320 × 320	6	0.5	Dependent on triggering	93.8	160	3:42 (dependent on respiratory frequency)
Axial, echo-planar diffusion-weighted (*b* = 50, 100, and 800 s/mm^2^)	120 × 150	6	0.6	Dependent on triggering	60.1	90	2:34 (dependent of respiratory frequency)

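### McNemar is planned without a stated unit of analysis, although patients contribute repeated US-SMS pairs; if screenings are pooled, the test ignores clustering within patients

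*Protocol article*

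**What the plan says.** The Statistical analysis section names one test for the accuracy comparison: "McNemar test will be used to determine significance in differences between the sensitivity and specificity of SMS" versus US. It names no unit and no handling of repeated screenings.

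The data are repeated by design. Study design: "Patients will be invited for paired US-SMS surveillance, every 6 months". Surveillance program: enrolled patients "receive paired US-SMS surveillance with a 6-month interval, with an inclusion period of 3 years".

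The Sample size calculation starts from patients: "This resulted in a calculated sample size of 470 assuming a drop-out rate of 10–15"%. It then adds that "we estimated that the average number of screenings will be 2.5 per patients", so that "the total number of screenings over the study period will be 1,175 screenings of paired US-SMS". Shortly afterwards it concludes that the cohort is large enough. The planning values are that "the prevalence of HCC in our screening population was set at 12"% and that "the sensitivity and specificity of the SMS protocol was assumed be 80% and 72%, respectively", against 53% and 91% for US.

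**The concern.** McNemar compares the two kinds of discordant pair and takes every pair as independent. Several pairs from one patient need not be. The Background section notes that obesity and steatohepatitis impair US access to the liver. That is a lasting feature of the patient which acts on US and not obviously on the short MRI (SMS). Such a feature makes the SMS-US difference similar from visit to visit.

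If the 1,175 screenings are entered as independent pairs, the variance of the specificity difference is likely understated. The p-value is then likely too small and any interval from the pooled screenings likely too narrow. Specificity, PPV and NPV belong to the primary endpoint, so the unit on which they are estimated should be fixed before results are seen. The sample size section counts patients and then cites screenings in support, and the article never links the two.

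**Working it through.** **1. The plan's own figures.** 470 × 2.5 = 1,175, as stated.

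For the 470, take one pair per patient, HCC in 12%, sensitivities 80% and 53%, tests independent given disease, and a two-sided exact McNemar test at 0.05 (the article does not give sidedness). Power is 0.807 at N = 470 and reaches 80% at about N = 465. So 470 reproduces as a number of evaluable patients, though by this route not as one already inflated for drop-out. An unpaired two-proportion route gives 47/0.12 = 392, or 461 after 15% drop-out. Both routes that come close count patients.

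**2. Design effect for pooled screenings.** Let ρ be the within-patient correlation of the SMS-US difference and m′ the size-weighted mean number of screenings per patient. Then D = 1 + (m′ − 1)ρ, and the actual size of a nominal 5% test is 2[1 − Φ(1.96/√D)]. With equal visits m′ = 2.5; with 1 to 6 visits averaging about 2.5, m′ = 3.25. The article gives no ρ, so the values below are assumptions.

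| ρ | D | Actual size |
|---|---|---|
| 0.1 | 1.15–1.23 | 7–8% |
| 0.2 | 1.30–1.45 | 9–10% |
| 0.3 | 1.45–1.67 | 10–13% |
| 0.5 | 1.75–2.12 | 14–18% |

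A correct interval for the specificity difference is √D times the unadjusted width: √1.30 = 1.14 to √2.12 = 1.46 for ρ from 0.2 to 0.5.

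**3. Simulation under equal specificity.** Setting: 414 patients without HCC (470 × 0.88), 1 to 6 screenings each, probit patient effects, specificities 72% to 91%, 2,000 runs. Size of the unadjusted exact McNemar test:

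| Latent correlation | Separate effects per test | Half shared | Fully shared |
|---|---|---|---|
| 0.2 | 5–8% | 4–6% | 4–5% |
| 0.4 | 9–11% | 7–8% | about 4% |

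A cluster-robust version stayed at about 4–6%. A second simulation used 400 patients, 1 to 4 screenings, mean false-positive probability 0.15, separate effects and 4,000 runs. At within-patient correlations of 0.2, 0.4 and 0.6 the unadjusted size was 10.5%, 15.6% and 18.3%; the cluster-robust size was 5.0%, 5.4% and 4.6%.

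**4. Effect at the planned specificities.** Non-HCC screenings: 1,175 × 0.88 = 1,034. With independence given disease, the discordant probabilities are 0.28 × 0.91 = 0.2548 and 0.72 × 0.09 = 0.0648, with sum 0.3196 and difference 0.19. Then z = 0.19 × √(1,034/0.3196) = 10.8. At D = 2.5, z = 10.8/√2.5 = 6.8. If 12% applies to patients and each HCC patient has one diseased screening, there are about 1,119 non-HCC screenings and z is about 11.2.

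**5. Where the verdict could change.** With the same discordance, the unadjusted standard error is √(0.3196/1,034) = 0.0176. An observed difference is unadjusted-significant from 1.96 × 0.0176 = 3.4 points. At D = 2.12 it needs 3.4 × 1.46 = 5.0 points. Only a difference between these two would be misjudged.

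**The case against.** A reader might infer that the article commits itself to McNemar on 1,175 pooled screenings, so that the specificity p-value is certainly too small. The text does not support this. No unit is named, 470 is the figure called the sample size, and it reproduces with one pair per patient. On that unit there is no clustering problem. The full protocol or an analysis plan, neither of which is shown, may already settle the matter.

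The direction is not certain either. What counts for McNemar is the correlation of the difference between tests, not of each test's false positives. If patient effects are shared equally by both tests, there is no inflation. The imaging criteria also weaken the idea of a benign lesion flagged at every visit: SMS counts only new or growing nodules, the first US criterion is similar, and the second exempts typical cysts. That second US item carries no condition of novelty or growth, however, so if the items are alternatives, a stable atypical nodule could recur on US alone.

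A reader might also infer that reducing to ever positive per patient must give false-alarm rates of 56% (1 − 0.72^2.5) and 21% (1 − 0.91^2.5). These hold only for independent screenings; positive correlation lowers both. Ever positive is also only one way to obtain one pair per patient.

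Finally, SMS is the test assumed to be less specific. An over-liberal test at the planned values would overstate its disadvantage, not create a claim in its favour.

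All of this stands, and it makes the point conditional. It does not remove it: the article names an independence-based test for data that it describes as repeated, and cites the repeated pairs shortly before judging the sample sufficient. Full sharing protects only the comparison; an interval for one test's own specificity would still be too narrow if that test's results correlate within patients.

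**Conclusion.** The point holds conditionally. The unit is not stated, and a plain McNemar test on pooled screenings would not allow for within-patient correlation. The size of the error rests on assumed correlations: about 4–5% actual type I error with fully shared patient effects, rising to about 18% with separate effects and a correlation of the difference of 0.5–0.6.

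At 72% versus 91% significance survives easily. Sensitivity, the comparison that reproduces the sample size, is little affected if each HCC patient contributes one pair. The harm is therefore to interval width for specificity, PPV and NPV, and to the verdict on specificity if the true gap is only a few points.

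**What to change.** In the Statistical analysis section, state the unit for each measure.

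- Sensitivity: one pair per HCC patient, taken at the round when HCC was first flagged, or at the last round before an interval cancer. McNemar is then appropriate.
- Specificity, PPV and NPV: per screening, with the patient as cluster, using a patient-clustered McNemar test (for specificity), GEE with robust standard errors, or a patient-level bootstrap.

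In the Sample size calculation, describe the 1,175 as clustered observations in 470 patients.

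This costs about a paragraph, needs standard software and no new data. The downside is somewhat wider confidence intervals.

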## Discussion

The aim of this study protocol is to evaluate the value of the SMS and compare it to the current standard of biannual US surveillance for HCC. This is a prospective multicenter study with a paired design for a single arm of patients.

Previous studies have proven the value of HCC imaging surveillance with US when compared to no screening [22, 23]. Jespen et al. [24] suggested that it may be necessary to perform more randomized controlled trials on HCC surveillance to determine whether the benefits of surveillance weigh up against the harms and the costs. A large scale randomized controlled trial showed that semiannual screening with US reduced HCC-related mortality by 37% for those who underwent surveillance, despite suboptimal adherence to the surveillance program (58.2%) [23]. Other studies have reinforced the benefits of surveillance in high-risk patients with detection of more early-stage HCC with consequently a higher rate of curative treatments and better survival than in the non-surveillance group [25, 26]. Kim et al. [27] and An et al. [28] have published study protocols based on abbreviated ncMRI protocols. Either the patients were offered an annual screening using ncMRI or were assigned to biannual US surveillance with a cross-over study design of biannual ncMRI surveillance or US [27, 28]. We believe that our study design of paired US-SMS will allow for a direct head-to-head comparison in diagnostics and patient acceptance.

To the best of our knowledge, this is the first published paired US-MRI study design. We expect that the proposed SMS will detect at least twice as many early-stage HCC lesions and be the next step in improving the hepatitis-cirrhosis HCC care chain. Based on our preliminary results and emerging insights from the literature, we expect the projected cost-effectiveness analysis to favor SMS [13–15]. We also expect the SMS to improve sensitivity for detection of early-stage HCC as an objective surveillance imaging tool, compared to US and may gain patient acceptance as a new standard for imaging surveillance of HCC.

